##### Domain of Clinical Variables

###### Diagnosis

The psychodynamic diagnosis was based on Operationalized Psychodynamic Diagnosis (OPD II), a multiaxial diagnostic system for psychodynamicaly oriented therapists and psychiatrists (41, 42).

###### Personality Assessment

The Personality Inventory for DSM-5 (Diagnostic and Statistical Manual of Mental Disorders) (PID-5)—Adult (43). A set of 25 core elements of personality description that combine in five broad domains of maladaptive personality variation: negative affect, detachment, antagonism, disinhibition, and psychoticism (43).

##### Domain of Psychosocial Variables

###### Psychosocial Stressors

The Life Events Questionnaire (LEQ) evaluates the occurrence of 14 stressful life events over the last 12 months and the impact of these events on the subject’s life. The LEQ also focuses on the stressors’ association with the onset of current psychiatric problems (44).

###### Therapeutic Alliance

The California Psychotherapy Alliance Scale (CALPAS) is a 24-item self-applicable questionnaire (45).

###### Defense Mechanism Style

The Defense Style Questionnaire (DSQ-40) is a 40-item self-applicable questionnaire that aims to identify derivatives of defense mechanisms (46).

###### Motivational Status

The University of Rhode Island Change Assessment (URICA) assesses motivation for change by providing scores on four stages of change: precontemplation, contemplation, action, and maintenance (47).

##### Domain of Other Variables

###### Religiosity

The Duke University Religion Index (DUREL) is a five-item measure of religious involvement. It was developed for use in large cross-sectional and longitudinal observational studies (48, 49). The World Health Organization Quality of Life Group—Spirituality, Religion, and Personal Beliefs (WHOQOL-SRPB BREF) is an abbreviated version of the WHOQOL-SRPB that assesses spiritual, religious, and personal beliefs within quality of life; respondents choose the most suitable item from each of the eight SRPB facets and the one spirituality item (*meaning of life*) located in the psychological domain of the WHOQOL-BREF (36, 50).

#### Sample Size Estimation

Our sample size calculation relied on the study of Schaf (51) using BDNF serum levels before and after psychotherapy as outcomes. We arrived at a number of 42 subjects for each psychotherapy and control group, considering a significance level of 5% and a power of 80% difference to be detected 0.22 with a standard deviation of 0.43 and losses of 20–30%. We estimated a total sample size of 126 patients and 42 blood donor healthy controls for biological variable (as comparative of BDNF samples). The inclusion criteria will include having started psychotherapy within 1 month, an age above 18 years, and a BDI score greater than 15. The exclusion criteria will include psychotic disorders, current use of psychoactive substances, cognitive deficits, and dementias.

The study will include a subsample of healthy controls for control of blood samples that were recruited from the HCPA blood bank. The exclusion criteria for the control group included conditions (current or past) that precluded participation in the study (e.g., psychiatric disorders and/or psychiatric treatments), immune disorders, use of immunosuppressants, anti-inflammatory drugs used for fewer than 3 weeks, smoking, abuse and/or drug addiction, and infectious diseases for fewer than 3 weeks.

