**Methods:**
*Design:* longitudinal, naturalistic. *Participants:* One hundred twenty-six patients who underwent one of three evidence-based modalities of individual psychotherapy [psychodynamic psychotherapy (PDT), interpersonal psychotherapy (IPT), and cognitive–behavioral psychotherapy (CBT)] were included. *Measure:* Primary outcomes are divided into three domains of variables: clinical (general psychiatric symptoms), biological (serum BDNF levels), and psychosocial (resilience, quality of life, coping strategies, social support, and quality of life-adjusted years of life). Confounding/mediator variables included clinical (personality traits, type of psychotherapy, number of sessions, concomitant use of pharmacological treatment, history of previous psychotherapeutic treatment, medical and psychiatric comorbidities, and psychiatric diagnosis), psychosocial (psychosocial stressors, therapeutic alliance, and defense mechanism style), and other (religiosity) factors. *Procedure:* The follow-up period will be baseline and 6 months and 1 year after entering the study. The study will include 42 controls for biological variables only. Sample size calculation considered a significance level of 5% and a power of 80% to detect a difference of 0.22 with a standard deviation of 0.43, assuming losses of 20–30% of patients. The comparison between the modalities of psychotherapy will be by generalized estimating equations (GEE) model, the analysis of mediators by the Hayes method, and confounders by multivariate logistic regression.

**Discussion:** The findings of this study are intended to demonstrate the outcomes of evidence-based psychotherapies for clinical, psychosocial, and biological parameters and to understand the mediators and confounders of this process in a real-life setting for patients with severe mental illness, thus contributing to the establishment of evidence-based public health policies in the field of psychological interventions.

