## Aims

Our primary aim is to evaluate the outcomes associated with different forms of individual psychotherapy [psychodynamic psychotherapy (PDT), interpersonal psychotherapy (IPT), and CBT] in a public outpatient clinic for mental disorders. Our primary outcomes are divided into three domains of variables: clinical (general psychiatric symptoms), biological (serum BDNF levels), and psychosocial (resilience, quality of life, social support, and quality of life-adjusted years of life).

Our secondary aim is to evaluate potential confounders/mediators/moderators for the main outcomes: personality traits, type of psychotherapy, number of sessions, the therapist’s duration of training, concomitant use of pharmacological treatment, history of previous psychotherapeutic treatment, medical and psychiatric comorbidities, psychiatric diagnosis, therapeutic alliance, and defense mechanisms.

Our main hypothesis is that all three modalities of therapy will produce reduction of symptoms in the clinical domain and improvement in the psychosocial domain. All psychotherapies will increase BDNF at 6 months of follow-up. As secondary hypotheses, the mechanisms of improvement will be mediated by the therapeutic alliance, motivational status, and defense mechanisms (for PDT). The confounders of this therapeutic improvement will be number of sessions, comorbidities, and medication use. The moderating factors will be gender, age, personality traits, religiosity, and defense mechanisms (for CBT).

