## Methods

### Design

The Longitudinal Investigation of Psychotherapy Outcome (LIPO) study will compare three modalities of psychotherapy (PDT, CBT, and IPT) in a longitudinal course, in a naturalistic setting. The choice of the three modalities of psychotherapy is evidence-based and listed in guidelines for indication of first-line treatment for depression (30, 31).

The evaluations will take place in three moments: in the baseline (until the fourth session of psychotherapy) and 6 and 12 months after entering the study. The invited participants will be the patients who are undergoing any psychotherapy in the outpatient clinic of the Hospital de Clínicas of Porto Alegre (HCPA).

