1.1 Clinical domain			
Depression symptoms (BDI)	X	X	X
Anxiety symptoms (BAI)	X	X	X
Psychiatric symptoms (SCL-90-R)	X	X	X

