### Procedure

The study will be disseminated through the presentation of its protocol in meetings with the outpatient services of the HCPA that refer patients to the psychiatry service, such as the internal medicine, pain, and bariatric surgery outpatient clinic.

The researchers will not participate in the indication of treatment of patients or in their assistance. Patients will be sought weekly in the HCPA outpatient medical records and through contact with resident physicians screening new patients. Those who fall into the eligibility criteria will be contacted by phone by the research assistant and invited to participate. It will be explained that refusal to participate will not entail any loss to the treatment. If they agree to participate, they will be asked to attend the HCPA Clinical Research Center (CPC-HCPA), where they will receive the informed consent form, sociodemographic interview, OPD interview, BDNF blood collection, and protocol with self-administered questionnaires. The consent form and OPD will be applied by the researchers. Patients will be contacted by telephone for the follow-up of 6 and 12 months (Figure 1).

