Limitations of this study include the heterogeneity of the training and experience of the resident psychiatrists and the absence of evaluation from their point of view in the psychotherapeutic process. As a study is naturalistic, there is no way to control the impact of the researchers’ interviews. We will collect a series of demographic data, use of medications, and number of sessions to control possible confounders, but we know that because it is an open study, there is no way to control all differences between groups. Also, psychotherapy studies often have large amounts of losses (16). To control this bias, we will compare the clinical and demographic characteristics of the lost sample with those that continue in relation to the baseline. As for the multiplicity of diagnoses that may be found, to homogenize the sample, we will consider for inclusion the BDI value >15.

Studies such as this one seek to contribute to the foundations of public health policies and investments for the treatment of patients with severe mental illnesses who are at risk of hospitalization and suicide. These types of investigations also seek to promote mental health, rehabilitation, and social reintegration. Understanding the mediating and biological mechanisms of the psychotherapeutic process can help to optimize these interventions and facilitate their indication according to the psychopathological profile and the severity of the patients.

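### Patients are selected on BDI >15 and then followed on BDI without an untreated group, so the plan cannot attribute the within-modality fall to therapy

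*Protocol article*

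**What the plan says.** The inclusion criteria, given in the article's Sample Size Estimation section, require "an age above 18 years, and a BDI score greater than 15". The Discussion repeats the cut-off and gives its purpose: "to homogenize the sample, we will consider for inclusion the BDI value >15". Table 1 lists BDI, BAI and SCL-90-R as primary outcomes of the clinical domain, each at baseline, 6 and 12 months. The Design section places the assessments "in the baseline (until the fourth session of psychotherapy) and 6 and 12 months after entering the study".

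The Aims state the main hypothesis as "all three modalities of therapy will produce reduction of symptoms in the clinical domain". The abstract likewise says that all the psychotherapies will improve clinical outcomes. The only group without therapy consists of healthy blood donors: "The study will include 42 controls for biological variables only". The Statistical Analysis section provides dependent t tests, non-parametric counterparts and GEE.

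On the order of events, the Procedure section says: "Those who fall into the eligibility criteria will be contacted by phone by the research assistant and invited to participate". The self-administered questionnaires follow at the research visit. No BDI before that visit is named, and the article does not say which BDI applies the cut-off.

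**The concern.** When patients enter because a score is high, part of that score is a temporary excursion. On average it is lower at the next measurement even if nothing has changed. Patients who seek help may also improve spontaneously over 6 to 12 months. A paired test or a GEE time effect compares the change with zero and so counts both as improvement. BAI and SCL-90-R are correlated with BDI and should show the same effect to a lesser degree.

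A comparison group with BDI follow-up would show how large this part is, but the study has none. At stake is the reading of the main clinical hypothesis: a fall in symptoms during therapy would be reported as one that therapy caused. The limitations in the Discussion cover training, the effect of the interviews, group differences and losses. They do not mention regression to the mean or natural course.

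**Working it through.** **The plan's own figure.** The only sample size is for BDNF: difference 0.22, SD 0.43, 5% two-sided, 80% power, 42 per group after losses of 20–30%. As a before/after calculation, n = (0.43 × (1.960 + 0.842) / 0.22)² = 30. With losses this becomes 30/0.8 = 38 to 30/0.7 = 43, which brackets 42. As a comparison of two groups, the same inputs give 2 × 30 = 60 per group before losses. The study is thus sized for change within a group, the kind of comparison in which regression to the mean does not cancel.

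**Inputs for BDI.** From the article: cut-off above 15 and a two-sided 5% test. With 42 per arm and losses of 20–30%, 29 to 34 complete; I use 32 per arm and 3 × 32 = 96 pooled. Assumed, because the article gives none of them: referred mean 20, SD 10, correlation over six months without a therapy effect r = 0.7, normal scores. The cut is placed at 15.5 for whole-number scores.

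**One score serves both purposes.**
- a = (15.5 − 20)/10 = −0.45; λ = φ(a)/(1 − Φ(a)) = 0.535. About 67% of referred patients qualify.
- Expected fall with no therapy effect = (1 − r) × SD × λ = 0.3 × 10 × 0.535 = 1.6 points.
- Variance of the qualifying score = 100 × (1 + aλ − λ²) = 47.3.
- Variance of change = (1 − r)² × 47.3 + (1 − r²) × 100 = 4.3 + 51 = 55.3, SD 7.43.
- Non-centrality = 1.61/7.43 × √n: 1.22 for n = 32 and 2.12 for n = 96.
- Chance of a significant fall (non-central t): 22% per arm and 55% pooled, against 2.5% in that direction under a true null.
- If the arms are independent, the chance that all three fall significantly is 0.22³, about 1%.

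**Separate qualifying and baseline scores.** Assume a screening-to-baseline correlation of 0.8 to 0.9, with 0.7 from either score to six months.
- Fall = (0.8 − 0.7) × 10 × 0.535 = 0.5 points, up to (0.9 − 0.7) × 10 × 0.535 = 1.1 points.
- Variance of change = 2 × 100 × 0.3 − (difference of the two correlations)² × (100 − 47.3), so SD 7.71 and 7.61.
- Chance per arm: 6% to 12%.
- This depends on how correlation decays. If the screening-to-six-month correlation is instead the product (0.8 × 0.7 = 0.56 or 0.9 × 0.7 = 0.63), the same formulas give falls of 1.3 and 1.4 points and chances of 15% and 18%. A separate baseline then helps less.

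**Range of assumptions, one score, 32 per arm, SD 8–10, r 0.5–0.8.**

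| Referred mean | Expected fall, points | Chance per arm |
|---|---|---|
| 15–22 | 0.6–4.2 | 9–71% |
| 25 | 0.4–1.5 | 6–14% |
| 30 | 0.1–0.8 | 3–6% |

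The direction is the same throughout. The size depends mainly on how many referred patients score near the cut-off.

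**The case against.** Four points on the other side carry weight.

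- **The baseline score may not be the qualifying score.** The Procedure section has eligibility known before the phone invitation and the questionnaires completed at the visit, which fits two separate scores. This stands as an open question. Separate scores reduce the bias but do not remove it, and natural course is unaffected.
- **The patients may score well above the cut-off.** The Introduction and Discussion describe complex and severe disorders in a tertiary centre, and at a referred mean of 25 to 30 the effect is small. This also stands, although referrals from pain and bariatric clinics could lower the mean.
- **BDI is not the only clinical outcome.** The abstract and Aims name general psychiatric symptoms, which the article measures with SCL-90-R. Patients are not selected on that scale, so it should regress less. Table 1 still lists BDI as primary.
- **The absence of untreated patients is a declared choice.** The Introduction concedes that longitudinal studies rank below randomized trials. That is fair, but it does not license a causal verb in the main hypothesis.

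A reader might infer that the main hypothesis is likely to be declared met with no therapy effect at all. The documents do not support that. The Aims require all three modalities to show the reduction, with psychosocial improvement as well, and the mid-case chance of three significant BDI falls is about 1%. The pooled 55% concerns a different claim, though a GEE time effect could report it. A reader might also infer that the comparison between modalities is distorted. The same cut-off applies to every arm, so regression largely cancels, and nothing in the text shows that scores fluctuate more in one modality.

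**Conclusion.** The point holds as a limit on what the study can conclude. Selection on BDI, BDI as a primary outcome, no untreated BDI follow-up and a causal hypothesis are all in the text, and they do not fit together. Some fall in BDI is expected without any therapy effect, and some in BAI and SCL-90-R to a lesser degree.

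The size cannot be fixed from the article. It ranges from negligible, if most referred patients score far above 15, to an amount that matters, if many score near 15 and one score serves both purposes. Every BDI figure given here rests on assumed means, SDs and correlations. This should be fixed, but it does not invalidate the study: a cohort can still describe change during therapy.

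**What to change.** 1. **Baseline.** State which BDI applies the cut-off. Apply BDI >15 to a BDI taken before the research visit, for example during the evaluation interviews. Measure change from the research-visit BDI, and keep patients whose visit score is 15 or lower. The cost is one repeat of a short self-report form and a smaller apparent improvement. The abstract speaks of patients already included; if it is too late for this step, report which score was used.
2. **Wording.** In the abstract and the Aims, restate the clinical hypothesis as symptoms falling during therapy, not as a reduction that therapy produces. In the Discussion's limitations, name regression to the mean and natural course as limits on that conclusion. This costs a few lines and is needed whatever is done about the baseline.

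Testing the observed fall against a computed expected fall is not a good main remedy: it needs a retest correlation without therapy, which this study cannot supply.

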### Participants

All patients included at the HCPA psychotherapy clinic will be evaluated by a fourth-year psychiatry resident with training in psychotherapy. Patients will be referred from the outpatient clinic of clinical psychiatry, pain medicine, or preoperative bariatric surgery. Each patient who agrees will undergo up to five evaluation interviews and engage in discussions with a supervisor. They will be next referred, based on clinical judgment, to the most suitable modality of psychotherapy. The clinic offers three methods of individual psychotherapy: PDP, IPT, and CBT.

The psychotherapy modality will be indicated by general criteria (17), considering the following characteristics: previous favorable experience with some kind of psychotherapy, psychological-mindedness, presence of personality disorder or traits, number of diagnoses of psychiatric disorders, and relief of symptoms. When diagnosed with personality disorder associated with one or more major psychiatric disorders and psychological-mindedness, PDT will be indicated. When there are up to two major psychiatric diagnoses without personality disorder, it will be directed to CBT as well as in the exclusive quest for symptom relief. When the focus of the problem is exclusively up to two of the following: 1) dispute, 2) roles dispute, 3) role transition, or 4) interpersonal deficits and no personality disorder, IPT will be indicated.

Psychotherapeutic care will be provided by psychiatry residents in their second, third, and fourth years of residency in psychiatry under weekly supervision of dialogued interviews. The residents have weekly theoretical seminars related to each of the psychotherapeutic techniques offered throughout the period of residence. They also engage in weekly clinical seminars in which patients are interviewed by teachers to prompt discussions about the clinical aspects related to cases. When there is doubt about patient management, the patient is interviewed by the supervisor.

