#### Confusion/Mediator/Moderator Factors

The mediating factors will be therapeutic alliance, motivation, and defense mechanisms (for PDT only). The moderating factors will be gender, age, religiosity, stressors, social support, personality traits, and defense mechanisms (for CBT and IPT). The confounding factors considered will be diagnosis, medication use, number of sessions, and comorbidities.

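### Controls, but not patients, are excluded for smoking, immune disorders, immunosuppressants, anti-inflammatory drugs and recent infection, so the auxiliary patient–control BDNF contrast may be confounded

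*Protocol article*

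**What the plan says.** Both eligibility lists stand in the section Sample Size Estimation of the protocol article.

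- **Controls.** They come from the hospital blood bank. Besides psychiatric disorder or treatment, the exclusions are "immune disorders, use of immunosuppressants, anti-inflammatory drugs used for fewer than 3 weeks, smoking, abuse and/or drug addiction". The last item on that list concerns recent illness: "and infectious diseases for fewer than 3 weeks".
- **Patients.** Inclusion requires "having started psychotherapy within 1 month, an age above 18 years, and a BDI score greater than 15". Then: "The exclusion criteria will include psychotic disorders, current use of psychoactive substances, cognitive deficits, and dementias".
- **Role of the controls.** The section plans "126 patients and 42 blood donor healthy controls for biological variable (as comparative of BDNF samples". The Abstract likewise limits the controls to the biological variables.
- **Source of patients.** Under Participants: "Patients will be referred from the outpatient clinic of clinical psychiatry, pain medicine, or preoperative bariatric surgery".
- **Planned confounders.** Under Confusion/Mediator/Moderator Factors: "The confounding factors considered will be diagnosis, medication use, number of sessions, and comorbidities".
- **Data collected.** Table 1 lists serum BDNF at baseline and 6 months, comorbidities at baseline, and pharmacological treatment at all three visits. The Procedure section adds a sociodemographic interview whose items are not shown.

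**The concern.** A healthy comparison group should differ from the patients in the condition under study and, as far as possible, in little else that could move the marker. Here a set of somatic and lifestyle factors is screened out of one side only. The controls have a single use, so a fault in their comparability falls on everything they are recruited for. If patients smoke, have immune disease, take anti-inflammatory or immunosuppressant drugs or have had a recent infection, a BDNF difference from controls may belong to those factors and not to mental disorder.

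The wording of the 3-week qualifier adds a smaller problem. As printed, it removes controls with short anti-inflammatory use or short infection and lets in those with long use or long infection. If an interval before blood sampling was meant, the text does not say so.

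**Working it through.** **Step 1: the two lists side by side.**

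| Factor | Control exclusion | Patient exclusion | Already collected in patients |
|---|---|---|---|
| Smoking | yes | not named | not listed; the interview may cover it |
| Immune disorders | yes | not named | comorbidities, baseline |
| Immunosuppressants | yes | not named | pharmacological treatment |
| Anti-inflammatory drugs | yes, with 3-week qualifier | not named | pharmacological treatment |
| Recent infection | yes, with 3-week qualifier | not named | not listed |
| Substance abuse | yes | current psychoactive substance use | roughly mirrored |

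Five factors are unequal and one is roughly balanced. Both lists are printed, so this is a stated design feature and not a detail left to a fuller document.

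**Step 2: which analyses use the controls.** The Aims section states the BDNF hypothesis as an increase at 6 months under every therapy, which is change within patients. The comparisons among the three therapies are between patients. Neither involves the controls. Only the patient–control contrast is exposed.

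**Step 3: can 0.22 and 0.43 scale the bias?** The inputs from Sample Size Estimation are a difference of 0.22, SD 0.43, 5% significance, 80% power and losses of 20–30%. The tests are two-tailed (Statistical Analysis).

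- As a before–after mean: n = (0.43 × (1.960 + 0.842) / 0.22)² = 30, or 32 with the t distribution. Allowing for losses, 30/0.75 = 40, 30/0.70 = 43, 32/0.80 = 40, 32/0.75 = 43, and 32 × 1.3 = 42. The stated 42 is reproduced.
- As two independent groups: n = 2 × (0.43 × 2.802 / 0.22)² = 60 per group before losses, 60/0.80 = 75 to 60/0.70 = 86 after. The stated 42 is not reproduced.

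The inputs therefore behave as the mean and SD of within-patient change, in line with the section's own statement that BDNF before and after psychotherapy was used. They give neither the between-person SD nor a target difference between patients and controls.

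**Step 4: illustration on assumed values only.** Suppose a share p of patients and no controls carry a factor that shifts BDNF by s between-person SDs. The spurious difference is p × s SD. With no true difference, a two-sided 5% test rejects with probability Φ(b/se − 1.96) + Φ(−b/se − 1.96), where b = p × s and se = √(1/n₁ + 1/n₂). The SD cancels, so 0.43 is not needed. The se is 0.218 for 42 v 42 and 0.178 for 126 v 42.

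| p | s | bias (SD) | rejects, 42 v 42 | rejects, 126 v 42 |
|---|---|---|---|---|
| 0.1 | 0.25 | 0.025 | 5.2% | 5.2% |
| 0.2 | 0.5 | 0.10 | 7.4% | 8.7% |
| 0.4 | 0.75 | 0.30 | 28.0% | 39.1% |

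The article gives neither p nor s, and s could have either sign. The range shows only that the effect could be negligible or material.

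**The case against.** The strongest reply is that the contrast is peripheral. No patient–control hypothesis is stated, and the sample size rests on change within patients. Comorbidities and medication are already recorded, so patients with immune disease or on the relevant drugs could be set aside at analysis. Table 1 is not exhaustive: age and gender are planned moderators and do not appear in it, so the sociodemographic interview may well cover smoking. The exclusion of patients using psychoactive substances might be read to include tobacco. A restricted comparison also sits uneasily with the naturalistic aim.

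Most of this stands, and it limits the point to one auxiliary contrast. It does not remove it. The control list names smoking separately from drug abuse, so the plain reading leaves patients who smoke eligible. The controls contain no smokers and nobody with an immune disorder by design, so the data support a comparison only among people without those factors; a covariate cannot supply the missing controls. The naturalistic aim concerns the patients' treatment and outcomes, and a restricted analysis reported alongside the full one does not disturb it.

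A reader might also infer that the article itself holds these factors to alter BDNF, or that it plans to read a rise after therapy as a return towards control values. It says neither. It gives no reason for the control criteria, which may simply define a healthy donor.

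**Conclusion.** The point holds in a limited form: the exclusion lists are unequal on five factors, and the patient–control BDNF contrast may be confounded by them. The within-patient hypothesis and the comparisons among therapies are unaffected. The point assumes that psychoactive substances do not include tobacco and that some patients carry the other factors. Referral from pain and bariatric clinics makes that plausible, but the article gives no frequencies.

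Three stronger readings are not supported:

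- **That the contrast is shown to be biased, by a known amount.** Size and direction cannot be derived, and expressing a bias or the power of this contrast through 0.22 and 0.43 would misuse before–after inputs.
- **That the imbalance cannot be dealt with afterwards.** Much of the information is already collected, and the rest may be.
- **That controls are free of anti-inflammatory use.** On the printed wording, longer-term users are admitted.

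**What to change.** - Make sure smoking and recent infection are recorded at each patient blood draw, alongside the comorbidities and medication already collected.
- Report the patient–control BDNF comparison also in patients who meet the control criteria (other than the psychiatric ones), adjusted for age and sex. Attribute a difference to mental disorder only if it holds there. Psychiatric medication remains a separate difference that this restriction does not remove; the Introduction itself links BDNF to antidepressants.
- Reconcile the 3-week wording for anti-inflammatory drugs and infection with the interval before sampling that is meant.

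The cost is a few questions at the blood draw, one extra analysis and a clarified phrase. The restricted subset will be smaller and its estimate less precise. By how much depends on how many patients carry the factors, which the article does not say.

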#### Statistical Analysis

Shapiro–Wilk test will be used to determine normality. For parametric distributions, dependent or independent *t* tests will be performed. To determine differences between categorical variables, the chi-squared test will be used. For nonparametric distributions, we will use the Wilcoxon test and Mann–Whitney *U* test to compare nonrelated and related means, respectively. A generalized estimating equations (GEE) model will be used to investigate multivariate repeated measurements. The Hayes method will be used to analyze the mediators (52), and the multivariate regression will be used to analyze the confounders. *Post hoc* analyses will be performed using the Bonferroni test.

The data will be expressed as mean ± standard deviation (SD), and a *p* value less than or equal to 0.05 will be considered to be statistically significant (two-tailed). The statistical analyses will be performed using the SPSS version 20.0 software package (IBM^®^, New York, USA).

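### The 3-week limits in the control exclusions are worded as length of exposure, not time before the blood draw, so as written they work against the list's evident purpose (minor)

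*Protocol article*

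**What the plan says.** The eligibility criteria for controls stand in the second paragraph of Sample Size Estimation in the protocol article. The study plans "42 blood donor healthy controls for biological variable (as comparative of BDNF samples"), described again as "healthy controls for control of blood samples that were recruited from the HCPA blood bank". The Abstract confirms that they serve the biological variables only.

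The exclusion list opens with "conditions (current or past) that precluded participation in the study (e.g., psychiatric disorders and/or psychiatric treatments), immune disorders, use of immunosuppressants" and continues with "anti-inflammatory drugs used for fewer than 3 weeks, smoking, abuse and/or drug addiction, and infectious diseases for fewer than 3 weeks". Two of these items carry a time limit: "anti-inflammatory drugs used for fewer than 3 weeks" and "infectious diseases for fewer than 3 weeks". No other section restates either item or refers it to the day of sampling.

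**The concern.** For a reference blood sample, what matters is whether the donor is under the influence of the drug or the infection when the blood is drawn. A limit on time since last exposure controls that. A limit on length of exposure does not, and with the sign used here (fewer than 3 weeks leads to exclusion) it selects the wrong donors.

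Serum BDNF is one of the three primary outcome domains, and the controls have no other function than to be its comparator. The authors evidently considered inflammation and infection worth removing from that comparator, or they would not have listed them. A printed rule that does not remove the long-running exposures fails at the one thing it is there to do. Another group also could not repeat the selection from it with confidence.

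**Working it through.** No quantity is disputed, so the check is mainly one of reading.

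**The one figure nearby, for context.** The article gives "a significance level of 5% and a power of 80% difference to be detected 0.22 with a standard deviation of 0.43 and losses of 20–30" percent, based on BDNF before and after psychotherapy, and arrives at 42 per group. As a paired comparison, two-sided 5%, power 80%:

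- n = (SD × (z₀.₉₇₅ + z₀.₈₀) / difference)² = (0.43 × (1.960 + 0.842) / 0.22)² = 29.98, so 30. The paired t version gives 32.
- With 20% losses: 30/0.80 = 37.5, so 38; 32/0.80 = 40.
- With 30% losses: 30/0.70 = 42.9, so 43; 32/0.70 = 45.7, so 46.

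The stated 42 lies inside this range. The exclusion wording does not enter the calculation, so correcting it leaves the number unchanged.

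**The two readings side by side.** The literal reading excludes when the length of exposure is under 3 weeks. The recency reading excludes when any exposure falls within the 3 weeks before blood collection. The donors below are illustrations, not cases from the article.

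| Donor | Literal reading | Recency reading |
|---|---|---|
| Anti-inflammatory for 2 days, ended long ago | excluded | not excluded |
| Anti-inflammatory for 2 days, within the last 3 weeks | excluded | excluded |
| Anti-inflammatory daily for 6 months, still taking it | not excluded | excluded |
| Infection of 1 week, resolved long ago | excluded | not excluded |
| Infection of 6 weeks, still present | not excluded | excluded |

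The readings agree on the recent short exposure. They disagree on the old short one and on the long ongoing one, each time in the direction that defeats the purpose. Suppose the items are instead taken to mean a current exposure that began less than 3 weeks ago. The old short exposures are then no longer excluded, but the long ongoing ones still get through.

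**What the rest of the list shows about purpose.** Immune disorders and immunosuppressant use are excluded whatever their length or date. A list that removes every immunosuppressant user is unlikely to be meant to keep a long-term anti-inflammatory user and reject a brief one.

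**Whether another item closes the gap.** The item on current or past conditions is open-ended, but its only examples are psychiatric. The items on immune disorders and immunosuppressants name neither anti-inflammatory drugs nor infection. The description as healthy blood donors may screen out some long exposures, but the article states no blood bank criteria, so the extent of that cover cannot be read from it.

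**The case against.** The strongest reply is that nobody would operate the rule literally. It would reject donors for any short course or brief infection in the past and keep those with long exposure, which makes no sense for healthy blood donors. The natural explanation is a translation slip for a 3-week window before sampling. The article has others of the kind: confounders appear as confusion factors in Table 1, and psychodynamic psychotherapy is abbreviated in two ways under Participants. This stands, and it is why the point concerns wording and not a faulty design choice. It does not remove the point, because a specific rule with a number in it is printed and nothing corrects it.

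The cover from the donor source and the immune exclusions also stands in part, as does the limited reach. The main BDNF hypothesis under Aims is a rise within patients at 6 months, the modalities are compared with one another by GEE, and the controls appear in no stated hypothesis.

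A reader might go further and infer that donors on long-term anti-inflammatories were in fact enrolled, that some number of the 42 is contaminated, that the reference BDNF level is shifted or noisier, or that controls already sampled should be dropped. The article supports none of this. It does not show how any donor was screened, gives no frequency of such exposures among donors, and reports no link between these exposures and serum BDNF.

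**Conclusion.** The point holds as a minor error of statement. The two time-limited exclusions for controls are written as durations with no link to the blood draw. As written, they exclude brief past exposures and do not exclude long-term ones, even when ongoing. That a recency window was meant is an inference from the neighbouring exclusions; the article does not say so.

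The reach is the 42-donor BDNF reference group. Patient eligibility, the sample size and the comparison between psychotherapies are untouched. No number of affected controls and no size or direction of effect on BDNF can be given. Any effect at all depends on screening staff having followed the literal text, which is unknown.

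**What to change.** Restate both items as time before blood collection, keeping the article's own 3 weeks: exclude a control with any anti-inflammatory use within the 3 weeks before sampling, whatever its length, and a control with any infection present or resolved within those 3 weeks.

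The article uses the past tense for the recruitment of controls and for their criteria, so some may already have been sampled. Check their screening forms to see which rule was applied.

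- If a recency window was used, correcting the text is enough and no control needs to be removed.
- If the literal rule was used, report the BDNF comparison without the controls who fail the corrected rule, and say so.

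The cost is one sentence and a review of at most 42 forms. In the second case a few controls may be lost from the reference group.
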